### Data and sample collection

Data and biological samples are collected during recruitment (28 weeks of gestation), at 1–3 d postpartum (within 72 h of delivery), and at scheduled visits 2, 3, and 4 (1.0–3.49 mo, 3.5–5.99 mo, 6.0–8.5 mo postpartum). Samples collected include human milk, and maternal and infant blood, urine, and stool. Additional data collected includes maternal and infant anthropometry, dietary intakes, and morbidity. A detailed timeline of data and sample collection is provided in **Figures 1** and **2**. To estimate milk volume, 3 sites (Bangladesh, Brazil, and The Gambia) are collecting saliva samples as described below using deuterated water. In Denmark, where this method is generally not acceptable, the mothers are instructed by the research team to test weigh the infant as described below.

**FIGURE 1 fig1:**
[figure not shown]
Mothers, Infants, and Lactation Quality Study timeline, questionnaires, and data and sample collection form schedule. ^1^3rd trimester. ^2^Late 3rd trimester, not done in Bangladesh. ^3^Maternal stool samples are not collected in Bangladesh. ^4^Not collected in Denmark. ^5^Only at visit 4 in The Gambia.

**FIGURE 2 fig2:**
[figure not shown]
Mothers, Infants, and Lactation Quality Study participant flow chart, for all 4 study sites. ^1^Denmark will use 24-h test weighing, instead of the Dose-to Mother deuterium method and saliva collections, for milk volume measurements. _C_, child; DBS, dried blood spots; _M_, mother.

#### Questionnaires

The field staff use standardized questionnaires designed for the MILQ Study. Participant's information, pregnancy screening, maternal dietary data, and socioeconomic data is retrieved during recruitment (at visit 2 in Denmark). Each of the following visits is equipped with their unique set of questionnaires (Figure 1).

#### Anthropometry

Anthropometry measures are especially important for excluding mothers who are under- or overweight and excluding malnourished infants with abnormal birth size and Z scores ≤2. The methods that are used to perform accurate, precise, and standardized anthropometric measurements are carried out by standard methods, with regularly validated equipment. The anthropometric measurements include:

Mother: weight, height, midupper arm circumference (MUAC) during pregnancy; (Denmark only at visit 2). Body composition using bioimpedance analysis (BIA) in Denmark and Brazil. BMI is calculated.Infant: weight, length, knee-heel length (in Denmark and The Gambia), MUAC, head circumference. Body composition is estimated from birth weight and length reported in health records, and by bioimpedance at visits 2, 3, and 4, in Brazil and Denmark, and by air displacement plethysmography until the infant reaches 8 kg,  (PEAPOD,  COSMED) in The Gambia. Z scores are calculated by the database system using WHO, 2006 growth standards

#### Milestones

Developmental milestones are evaluated at visits 3 and 4 to identify any infants with poor development, and to support the evidence that the milk MN concentrations are adequate for normal development. The final assessments at visit 4 includes Milestones (also collected at visit 3) and the Ages and Stages Questionnaires (19) (also administered at visits 2 and 3 in Brazil). Failure to meet normal developmental milestones in ≥2 domains will be considered abnormal during data analysis.

#### Dietary data

Dietary assessment of the mother is made by 2, 24-h recalls per period (visits 2, 3, and 4), and during pregnancy in Brazil and Denmark. One is taken during the study visits and the other during the week (≤10 d) before or after the study visit but not on an adjacent day. Data is collected about foods consumed the previous day based on a locally validated method. All sites have locally established procedures for food and nutrient intake assessment. Ideally, the total 6 d of recall data should reflect typical days of food intake, which may include weekend day(s). Data on the nutrient intakes of the mother enables classification of each woman based on the percent inadequate intakes (i.e. intakes below the Estimated Adequate Requirement) for each MN (calculated with the Intake Modeling, Assessment and Planning Program [IMAPP] software program), comparison between maternal intake and milk concentrations of MNs and other constituents, and comparison across sites.

### Specimen collection

All sample collection procedures have been developed with all field sites and collaborators at the analytical sites to ensure adequate sample collection (procedures and materials needed) for all planned analyses and are described in detail in the internal MILQ Study's “Manual of Operations and Procedures.” This detailed document has been shared with all field sites as the sample collection protocol, which included a completed sample collection form that states the specimen collected, subject ID, day and time, time of last meal, time of last feed, and volume and aliquots collected. All specimen collections are carried out under dim light or reduced light exposure. All samples are processed immediately and stored at –80°C until shipment to the analytical sites.

#### Colostrum

Colostrum is collected for antigen and MN analyses, with specifics to be determined based on volumes collected. At least 0.5 mL of colostrum is collected by manual expression from all women preferably 24–48 h after birth, but 48–72 h postpartum is acceptable. After cleaning the breast with mineral-free soap towelettes or deionized water, the sample is collected either into a collection tube or directly into a 2 mL amber storage tube. Samples collected by the mother at home are stored in the home freezer at −18°C until the first clinic visit.

#### Human milk and RNA

Milk samples at visits 2, 3, and 4 are collected preferably from the breast opposite from the one that the infant last fed from, using the Symphony electronic hospital-grade breast pump (Medela) for a full-breast expression. In the event of pump failure, milk is expressed using a hand pump or with manual expression, and noted on the collection form. The breast used for collection is cleaned with a mineral-free soap towelette or deionized water prior to milk expression. If ≥25mL of milk cannot be obtained from the first breast, the second breast is used to obtain a second full-breast expression, which will be noted on the collection form. A second milk sample from a subset of 50 women per study site is collected according to the protocol at visits 2, and 3, in Bangladesh, Brazil, and The Gambia, ∼2 wk after the respective main visit study, in order to estimate intraindividual variability in milk composition.

Milk RNA is collected in Denmark and The Gambia; 10 mL of the full-breast expression is used for RNA extraction. Under sterile conditions, the milk is centrifuged to obtain the RNA pellet, which is washed with PBS and stored under TRIzol in a DNA/RNA-free tube at –80°C. RNA is collected from 250 women at visit 2, and 50 women at visit 3 and visit 4, at both field sites.

#### Saliva and milk intake measurements

In the same periods that milk is collected, milk volume is measured in all women at each site, to determine how usual milk volume, which varies greatly among women, is related to nutrient concentrations and to enable estimation of total daily nutrient intake by the infant. Three of the field sites (Bangladesh, Brazil, and The Gambia) are using the International Atomic Energy Agency (IAEA) mother to child deuterium (D2M) method (https://www-pub.iaea.org/MTCD/Publications/PDF/Pub1429_web.pdf). Deuterated water (30 g) is administered to the mothers at visits 2, 3, and 4 and maternal and infant saliva samples collected at baseline, 1, 2, 3, 4, 13, and 14 d after dosing. Saliva samples are obtained from both mothers and infants, who are both weighed at baseline and day 14. Cotton balls are placed in the infant's mouth which are then squeezed by a syringe to retrieve the saliva. Denmark is estimating milk volume via 24-h test weighing of the infant before and after every feed for 24 h, plus 1 extra feed, to determine the 24-h intake. The infants are weighed with the same clothes and diaper at both weighings. Mothers are instructed by study personnel.

#### Blood

A venous blood sample is collected into an EDTA vacutainer from the mother on visits 2, 3, and 4. Fasting overnight or for 3–4 h prior to blood collection was ideal if possible. The mother's recall of the time of her last meal is recorded. A venous sample is collected from all infants at visit 2, and to reduce the number of infant blood draws to a total of 2, from 50% of infants at visit 3 and the other 50% at visit 4, randomly selected. In The Gambia, however, 100% of infants are sampled at each visit as well as the mother during pregnancy. The mother's recall of the time of the infant's last meal is also recorded.

Plasma is obtained by centrifugation of the blood sample at 1500 × *g* for 10 min at 4°C. The plasma is stored in aliquots in amber tubes. The buffy coat is collected into a DNAse/RNAse-free, sterile tube. The volume of the remaining RBCs is determined in order to wash the RBCs with an equal volume of 0.9% saline solution. The RBCs are centrifuged again and the supernatant is removed. This procedure is repeated until the supernatant is clear. After diluting with equal amounts of deionized water, the washed RBCs are aliquoted into amber tubes for storage. All aliquots are then frozen and stored at 70°C until analysis.

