#### Dried blood spots

Dried blood spots (DBS) are obtained for iodine status assessment. Four (infant) or 6 (mother) spots are prepared on filter paper cards using 50 µL of whole blood from the EDTA vacutainer used for blood collection. If insufficient blood volume is obtained, 1 DBS is prepared. The blood is dispensed onto the filter paper without touching the paper, and after a drying period of 24 h at ≤25°C, the cards are stored in bags without the DBS touching each other. The DBS can be stored at –20°C until shipment.

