	Tryptophan (amino acid, B-3-related)						
	Pantothenic acid (B-5)						
	Pyridoxal (B-6)						
	Pyridoxine (B-6)						
	Pyridoxamine (B-6)						
	Pyridoxal 5-phosphate (B-6)						
	Biotin (B-7)						
	Folic acid (B-9)						
	5-methyl tetrahydrofolate (B-9)					CPBA^2^	(34)
	Cobalamin (B-12)	X	X^P^			CPBA	(28, 35)
Choline and related	Choline	X	X^P^			UPLC-MS/MS	(36)
metabolites	Phosphocholine						
	Glycerophospho choline						
	Betaine						
	Carnitine						
	Creatinine						
	Dimethylglycine						
	Methionine						
	Trimethylamine N-oxide						
B-12 biomarkers	Methylmalonic acid		X^P^			UPLC-MS/MS	(37)
	Homocysteine		X^P^			HPLC-FLD	(38)
Minerals and	Iron	X	X^P^			ICP-MS	(39)
trace elements	Copper						
	Zinc						
	Selenium						
	Sodium						
	Potassium						
	Magnesium						
	Calcium						
Iodine status	Iodine	X		X		ICP-MS	(40)
	Thyroglobulin		X^DBS^			ELISA	(41)
	Thyroid-stimulated hormone						
	Total thyroxine						
Macronutrients	Protein	X				NIR-spectroscopy	(42)
	Fat						
	Carbohydrates						
Glycomics	Human milk oligosaccharides^3^	X				HPLC Chip/TOF-MS	(43)
	Human milk proteomics^4^	X				UPLC-QqQ-MS	(44)
Metabolomics	Biocrates MxP® QUANT 500^3^	X	X^P^			UPLC-MS/MS	(45)
Inflammation markers	α-1-acid glycoprotein (AGP)		X^P^			CPBA	(46)
	C-reactive protein (CRP)						(47)
	IL-1β, IL-4, IL-8, IL-6, IL-10, IL-33, TNF-α, IFN-γ	X	X			MSD immunoassay plates	(48)
Iron status	Soluble transferrin receptors		X^P^			CPBA	(49)
	Ferritin						(50)
Hormones	Leptin, insulin, and adiponectin	X	X			MSD immunoassay plates	(48)
Genetics	Single nucleotide polymorphism		X^B^			GWAS	(51)
	CpG methylation patterns		X^B^			EWAS	(52)
Microbiome	Microbial community				X	16s RNA sequencing	(53)
					X	Shotgun metagenomics	(54)
Transcriptomics	mRNA transcriptome	X^RNA^				RNA seq	(55, 56)

Analyzed in: ^B^buffy coat, ^DBS^dried blood spots, ^P^plasma, ^R^RBCs, ^RNA^RNA.

1 References that describe methods used for the analysis or on which the nonpublished methods are based on: CPBA, competitive protein binding assay; EWAS, epigenome-wide association; FLD, fluorescence detection; GWAS, genome-wide associations; ICP, inductively coupled plasma MS/MS; MSD, Meso Scale Discovery; MWL, multi-wavelength detection; NIR, near infra red; QqQ-MS, triple quad MS; TOF, time of flight; UPLC, ultra-performance-LC.

2 Plasma folate is analyzed by CPBA.

3
https://[name].faculty.ucdavis.edu/research/nutritional-glycomics/.

4
https://biocrates.com/mxp-quant-500-kit/.

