For maternal and infant blood variables, it is likely that blood samples will not be available from all participants, so the sample size will be reduced by necessity. However, if it is determined that it's acceptable to pool information from ≥2 study sites to construct RVs for infant blood variables, the precision of the estimate will be acceptable.

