### Additional study outcomes

Besides the primary study outcome, the construction of the RVs, secondary study outcomes are included in the study design and categorized into outcomes that: *1*) will be used for the construction of the RVs, *2*) will not be used to construct RVs, and *3*) country-specific measurements that are not used for RV development. These outcomes are summarized by category in **Table 6**.

**TABLE 6 tbl6:** Secondary outcomes of the Mothers, Infants, and Lactation Quality (MILQ) Study

Outcome category^1^	Bangladesh	Brazil	Denmark	The Gambia
Used for	Macronutrients, human milk oligosaccharides, peptides, and proteins, metabolomics			
constructing RVs	Micronutrient status of mothers and infants assessed in blood samples			
	Milk volume by D_2_O		24-h infant test weighing	Milk volume by D_2_O
	Iodine and maternal and infant iodine status biomarker			
Not used for	Maternal and infant dietary intakes			
constructing RVs	Maternal and infant anthropometry			
		Maternal body composition (bioimpedance)		
		Infant body composition (bioimpedance)		Infant body composition
				(air displacement plethysmography)
	Maternal and infant morbidity			
	Infant motor development assessment (3.5–5.9 and 6–8.5 mo pp)^2^			
	Infant development using the Ages and Stages questionnaire (6–8.5 mo pp)			
	Infant microbiome			
	Maternal inflammatory markers (28–30 weeks of gestation)			
Country-specific outcomes		Maternal nutrient intake at 35–37 weeks of gestation		
		Maternal microbiome^3^		Maternal microbiome^3^
			Maternal hemoglobin A1c^4^	
			Maternal markers of insulin sensitivity^5^	
			Maternal lipid panel^6^	

1 Unless otherwise stated, the time periods for the secondary outcome and analysis objectives are identical to those for the primary outcome (1–3.4, 3.5–5.9, 6–8.5 mo postpartum).

2 Based on WHO's motor milestones.

3 28–40 weeks of gestation, and 1 to 8.5 mo pp.

4 28–30 weeks of gestation, measured in whole blood.

5 28–30 weeks of gestation: insulin, C-peptide, and leptin (plasma).

6 28–30 weeks of gestation: total cholesterol, HDL-cholesterol, LDL-cholesterol, very LDL-cholesterol, and triglycerides (plasma). D_2_O, deuterated water; pp, postpartum, RV, reference value.

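### Table 4 plans plasma sodium and potassium, but the only blood tube named is EDTA, whose additive contaminates one of the two; milk values are unaffected

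*Protocol article*

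**What the plan says.** The *Blood* section of the protocol article states: "A venous blood sample is collected into an EDTA vacutainer from the mother on visits 2, 3, and 4". It continues: "Plasma is obtained by centrifugation of the blood sample at 1500 × *g* for 10 min at 4°C". The tube for infants is not named there, but *Dried blood spots* says that the infant and maternal spots are prepared "using 50 µL of whole blood from the EDTA vacutainer used for blood collection", so infant blood also goes into EDTA. No other blood tube appears in the article, and the EDTA salt is not given.

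Table 4 lists eight elements under minerals and trace elements: iron, copper, zinc, selenium, sodium, potassium, magnesium and calcium. The milk and plasma marks and the method (ICP-MS) stand once, on the first row: "Minerals and Iron X X^P^ ICP-MS (39". The footnote explains the superscripts: "Analyzed in: ^B^buffy coat, ^DBS^dried blood spots, ^P^plasma, ^R^RBCs, ^RNA^RNA". No exception is given for sodium or potassium.

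On the use of blood results, *Estimating centiles* says that precision will be acceptable if two or more sites can be pooled to "construct RVs for infant blood variables". Table 6 places "Micronutrient status of mothers and infants assessed in blood samples" among the secondary outcomes used for constructing RVs. The *Data analysis plan* says that criteria for nutritional status will be created and that children who fail them will be left out of the RVs. None of these three places names plasma sodium or potassium.

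**The concern.** EDTA in blood tubes is supplied as a dipotassium, tripotassium or disodium salt. ICP-MS measures the total amount of an element and cannot separate what came from the subject from what came from the tube. The article therefore fixes a tube and an analyte list that do not fit together: one of the two cations must be contaminated, whichever salt is used.

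At stake is the validity of one secondary plasma analyte. If its values were turned into blood centiles, they would describe the additive and the fill volume as much as the subjects. If they were used as a status criterion, some exclusions would depend on how full the tube was. The article does not commit to either use, so both consequences are conditional.

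**Working it through.** The plan gives no figure on this point to reproduce. The check has two parts.

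**1. Does the plan call for plasma sodium and potassium?** Only the iron row carries the marks. If they applied to iron alone, the other seven elements would have no matrix at all, not even milk. The fat-soluble vitamin and choline groups use the same layout, with one mark at the head of the group. The group reading is the only workable one, so sodium and potassium are listed for plasma, and the only plasma described comes from the EDTA tube.

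**2. How large is the contamination?** All inputs here are assumptions; none is in the documents.

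- Additive dose: 1.5–2.2 mg per mL blood
- Haematocrit: 0.35–0.40
- Dipotassium EDTA dihydrate: 404.5 g/mol, two potassium ions per molecule
- Added cation stays in plasma
- Physiological plasma level: potassium about 4 mmol/L (range 3.5–5.0), sodium about 140 mmol/L (range 135–145)

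Added cation in plasma (mmol/L) = dose (mg/mL) ÷ molar mass × 1000 × cations per molecule ÷ (1 − haematocrit).

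- Low end: 1.5 ÷ 404.5 × 1000 × 2 = 7.42 per litre of blood; ÷ 0.65 = 11.4 mmol/L.
- High end: 2.2 ÷ 404.5 × 1000 × 2 = 10.88; ÷ 0.60 = 18.1 mmol/L.
- Additive share of measured potassium: 11.4 ÷ 15.4 = 74% to 18.1 ÷ 22.1 = 82%.
- The same molar load from a disodium salt: 11.4 ÷ 140 = 8% to 18.1 ÷ 140 = 13% added to sodium.

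With a different range of inputs (1.2–2.0 mg/mL, haematocrit 0.35–0.45, each salt's own molar mass):

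| Salt | Added to plasma, mmol/L | Relative to physiological level |
|---|---|---|
| Dipotassium | 9.1–18.0 | 1.8–5.1 times |
| Tripotassium | 13.6–26.8 | 2.7–7.7 times |
| Disodium | 9.9–19.5 | 7–14% |

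**Can a constant be subtracted?** A tube holds a fixed mass of additive, so the dose per mL rises as the fill falls. Take 1.8 mg/mL at full fill and haematocrit 0.38.

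- Full tube: 1.8 ÷ 404.5 × 1000 × 2 = 8.90; ÷ 0.62 = 14.4 mmol/L.
- Tube 90% full: 14.35 ÷ 0.9 = 15.9 mmol/L. The extra 1.6 mmol/L already exceeds the whole assumed potassium range of 1.5 mmol/L (3.5 to 5.0).
- Half-full tube: 14.35 ÷ 0.5 = 28.7 mmol/L.

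A fixed correction would therefore fail for potassium even with small differences in fill. For sodium, the same 10% underfill shifts the value by about 1.6 mmol/L against an assumed normal width of 10 mmol/L, which is less severe. The uncorrected sodium bias (11.4–18.1 mmol/L) is still wider than that range. Short draws are foreseen: *Dried blood spots* provides for a single spot when blood volume is insufficient.

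**The case against.** Four objections deserve weight.

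- **Table 4 is coarse.** The riboflavin row carries one set of marks above a long list of vitamers, and a footnote then corrects the method for plasma folate. A group mark is thus weaker evidence for each single analyte than an explicit entry. That is fair, but Table 4 makes no exception for the two elements that need one, and no narrower reading of the mineral group works.
- **Collection details are kept elsewhere.** The article says that procedures "are described in detail in the internal MILQ Study's “Manual of Operations and Procedures", which is not shown. It may name another tube for minerals, and a condensed article need not name the tube salt. This stands as far as the missing salt goes: its absence is no fault in itself. It does not remove the mismatch, because the article states both the tube and the analyte list. If another tube is used, the article's account of blood collection needs that one correction.
- **A reader might infer that the milk RVs are damaged, with infants sorted in or out by tube fill.** The documents do not support this. Milk does not enter the tube. The status criteria are still to be created and name no biomarker; Table 6 speaks of micronutrient status without listing elements; infant blood RVs depend on pooling. No fill volumes or site differences in fill are given.
- **A reader might infer that whichever cation is affected cannot be derived at all.** That fits a potassium salt. With a sodium salt, sodium is biased by roughly a tenth, which is material but does not erase the signal. Nor does the point reach the cation that is absent from the salt, or the other six elements.

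**Conclusion.** The point holds as a minor error in the article as written. Following the stated tube and analyte list gives a contaminated plasma value for one cation: uninterpretable potassium if the salt is potassium, or sodium biased upward by roughly 8–13% if it is sodium. The direction rests on the general chemistry of EDTA tubes and on the group reading of Table 4; the size rests on the assumed dose, haematocrit and physiological levels. Across the ranges tried, potassium from a potassium salt was never usable.

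Milk sodium and potassium stand as planned. Harm to blood RVs or to the selection of children for the milk RVs would arise only if the contaminated plasma value were used there, which the documents do not say.

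**What to change.** In Table 4, limit the cation of the EDTA salt in use to milk: potassium for a dipotassium or tripotassium salt, sodium for a disodium salt. Alternatively, if plasma minerals come from a non-EDTA tube, say so in the *Blood* section. In either case, do not use a plasma value of that cation from EDTA blood in any blood RV, or in the nutritional-status criteria to be created under the *Data analysis plan*.

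The cost is a change of wording, with no change to samples or procedures. The downside is that one secondary plasma analyte is dropped; its milk counterpart remains.

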#### Dried blood spots

Dried blood spots (DBS) are obtained for iodine status assessment. Four (infant) or 6 (mother) spots are prepared on filter paper cards using 50 µL of whole blood from the EDTA vacutainer used for blood collection. If insufficient blood volume is obtained, 1 DBS is prepared. The blood is dispensed onto the filter paper without touching the paper, and after a drying period of 24 h at ≤25°C, the cards are stored in bags without the DBS touching each other. The DBS can be stored at –20°C until shipment.

#### Urine

Maternal and infant urine is collected to assess iodine status across sites, which will likely vary depending on consumption of locally fortified foods, e.g. iodized salt. Population daily iodine intake will be estimated from spot urinary iodine and creatinine concentrations. A midstream clean catch specimen is collected from the mother at the first voiding of the bladder during each visit. Infant urine collection is enabled using a cotton ball, pads, or urine collection bags that are placed inside a disposable diaper. The wet but not soiled (with feces) cotton ball or pad is removed from the diaper and the urine is obtained by squeezing the cotton balls in a syringe, or by squeezing the pad in a plastic bag with a missing corner. The urine is collected into a beaker and 2 aliquots from both the mother and infant urine are stored for iodine assessment.

